## Abstract

**Background:**

Guided by intersectionality frameworks, researchers have documented health disparities at the intersection of multiple axes of social status and position, particularly race and ethnicity, gender, and sexual orientation. To advance from identifying to intervening in such intersectional health disparities, studies that examine the underlying mechanisms are required. Although much research demonstrates the negative health impacts of perceived discrimination along single axes, quantitative approaches to assessing the role of discrimination in generating intersectional health disparities remain in their infancy. Members of our team recently introduced the Intersectional Discrimination Index (InDI) to address this gap. The InDI comprises three measures of enacted (day-to-day and major) and anticipated discrimination. These attribution-free measures ask about experiences of mistreatment *because of who you are*. These measures show promise for intersectional health disparities research but require further validation across intersectional groups and languages. In addition, the proposal to remove attributions is controversial, and no direct comparison has ever been conducted.

**Objective:**

This study aims to cognitively and psychometrically evaluate the InDI in English and Spanish and determine whether attributions should be included.

**Methods:**

The study will draw on a preliminary validation data set and three original sequentially collected sources of data: qualitative cognitive interviews in English and Spanish with a sample purposively recruited across intersecting social status and position (gender, sexual orientation, race and ethnicity, socioeconomic status, age, and nativity); a Spanish quantitative survey (n=500; 250/500, 50% sexual and gender minorities); and an English quantitative survey (n=3000), with quota sampling by race and ethnicity (Black, Latino/a/x, and White), sexual or gender minority status, and gender.

**Results:**

The study was funded by the National Institute on Minority Health and Health Disparities in May 2021, and data collection began in July 2021.

**Conclusions:**

The key deliverables of the study will be bilingual measures of anticipated, day-to-day, and major discrimination validated for multiple health disparity populations using qualitative, quantitative, and mixed methods.

**International Registered Report Identifier (IRRID):**

PRR1-10.2196/30987

## Introduction

### Health Disparities

Disparities in health status and access to care along single axes of social status and position (SSP), such as race and ethnicity, gender, and sexual orientation, are well documented in the United States [1,2]. Informed by intersectionality frameworks, recent research has emphasized disparities at the intersection of multiple axes of SSP. Intersectionality is rooted in Black feminist scholarship [3-5] and has become a central framework for public health efforts to understand and intervene in multiple, interacting, and context-dependent forms of social and health advantage and disadvantage [6,7]. Intersectional health disparities research allows for independent estimation of outcomes across intersections, acknowledging that groups at particular SSP intersections may experience better or poorer health than that predicted by nonintersectionally combining the effects of individual SSP. Examples include HIV infection among Black sexual minority men and transgender women [8], smoking among Asian or Pacific Islander sexual minority women [9], opioid misuse among high-income Black women [10], and hypertension among Black and Latina women [11].

### Health Impacts of Perceived Discrimination

A robust literature demonstrates that perceived, self-reported discrimination is associated with poorer mental and physical health, with most studies focusing on the health impacts of racial and ethnic discrimination among people of color and, to a lesser extent, sexuality- and gender-based discrimination among lesbian, gay, bisexual, and transgender people [12-15]. Perceived discrimination, including acute *major* events, chronic *day-to-day* discrimination, and anticipated discrimination, are thought to primarily impact health through (1) stress processes resulting in distress or health-harming coping strategies, and (2) physiological reactions such as elevated blood pressure and dysregulated hypothalamic-pituitary-adrenal axis function, which elevate cardiovascular disease risks [16-20]. Although not amenable to self-reporting and thus beyond the scope of this project, structural forms of oppression, such as residential segregation and lack of legal protection, set the context for perceived discrimination and drive poor health [21,22].

### Need for Intersectional Discrimination Measures

Quantitative intersectionality studies have burgeoned in the last decade and have largely focused on describing inequalities across groups cross stratified by SSP, taking an intercategorical [6] approach by examining outcomes across multiple intersecting SSPs [23,24]. In contrast, intersectional studies of the mechanisms potentially underlying health disparities have largely been intracategorical studies, focusing on experiences at a particular intersection [25,26]. Recognizing the conceptual bias inherent in using within-group analyses to make inferences about between-group differences [27,28], we and others have called for analytic approaches to *intercategorical* intersectionality to identify modifiable processes, including discrimination, that lead to health disparities [27-30]. Such studies require discrimination measures whose estimates are meaningfully comparable across intersectional groups. Previous intercategorical studies have adopted measures of racial and ethnic discrimination [31-36] that may not have content validity for other types of discrimination, or even for diverse racial and ethnic groups [37,38]. In fact, recent evidence shows that traditional scales of discrimination may not provide meaningful estimates of perceived general or racial and ethnic discrimination across diverse groups in the United States [39].

### Intersectional Discrimination Index

The Intersectional Discrimination Index (InDI) is a set of three measures of anticipated (InDI-A) and enacted (day-to-day [InDI-D] and major [InDI-M]) discrimination, originally designed for cross-group use. Notably, although anticipated discrimination is associated with mental health and cardiovascular stress responses [40,41], it is rarely measured [42]; the InDI-A is the first scale to measure this construct across multiple SSP. The InDI asks about discrimination *because of who you are* but without requesting attributions to specific SSP. Rather, these measures can be analyzed using cross-stratified demographic data. In 2019, our team published a binational study that provided preliminary evidence of the measures’ construct validity and test-retest reliability. Among participants in the United States (n=1518) and Canada (n=1065), as hypothesized, people of color and sexual and gender minorities (SGMs) reported higher levels of perceived discrimination, lifetime and past-year discrimination were associated with psychological distress, and enacted discrimination was correlated with the Everyday and Major Discrimination scales [43,44]. Test-retest reliability at 6 weeks was 0.70-0.72, similar to or higher than comparable measures [45,46].

The preliminary InDI study was published alongside four invited commentaries that identified the strengths of the InDI as well as areas requiring further study to clarify its utility for intersectional health disparities research [25,47-49]. Qualitative research using cognitive interviewing would reveal how respondents understand and respond to items in relation to multiple SSPs, identifying items that may require revision [48]. Psychometric analyses are needed to further validate the InDI measures across intersectional groups, including the assessment of configural, metric, and scalar properties (eg, factor structure, item loadings, and item intercepts) and measurement equivalence [26,47]. The preliminary InDI study was ethnically and racially diverse but had small sample sizes at specific intersections (eg, 50 Black SGM in the combined US and Canada sample), precluding intersectional validation analyses. In addition, Spanish measures are essential for health disparities research in the United States but need to be assessed for conceptual, semantic, and measurement equivalence to allow valid data pooling and comparison [50,51]. This is critically important given evidence of systematic response differences to discrimination measures by survey language and acculturation among Latino/a/x persons [52,53].

### Asking for Attribution in Intersectional Discrimination Measures

To date, intercategorical, intersectional discrimination studies have adapted extant measures to permit multiple attributions [31-36]. Research has highlighted attributional ambiguity among individuals situated at the intersection of marginalized SSP [54-56]. Allowing multiple attributions may not reduce cognitive burden or improve measurement validity; for example, conceptual slippage between SSPs may make participant selections arbitrary [56]. Options for quantitatively modeling attributions are limited because they are not tied to frequencies; this has resulted in analyses that either dichotomize discrimination or count attributions [31-36,57], representing losses of information on dose-response relationships [58] and on the complexity of experiences at particular intersections [26]. Therefore, the InDI was designed to be attribution free. This decision rests on a lack of evidence that the health impacts of discrimination depend on attribution. Some researchers have argued that a different construct underlies measures of discrimination that include attributions to perceived discrimination compared with those that do not [59], but no study has empirically tested the validity of this claim. Indeed, a 2015 review noted that the few studies comparing attributed and unattributed (racial and ethnic) discrimination measures have compared *apples and oranges* (ie, measures that reflect different constructs); the authors called for direct comparisons, including cognitive interviewing [18]. Further, some research participants reported the ability to unambiguously attribute discrimination to one or more SSP, and health disparities researchers remain interested in the burden and consequences of specific discrimination types [47,56]. Thus, we will conduct an evaluation inclusive of participant perspectives, examination of the degree to which SSP and attributions overlap, and direct comparison of correlations with health outcomes.

### Objectives

The primary aims of the study are to (1) assess the content and wording of the InDI measures (InDI-A, InDI-D, InDI-M) in English and Spanish; (2) evaluate the InDI measures’ configural, metric, and scalar structures, as well as their measurement equivalence across language and intersecting SSP; and (3) determine whether attributions should be included in the InDI measures.

## Methods

### Overview of Study Design

As described in Table 1, the study will draw on the preliminary validation data set and three original data sources.

**Table 1 table1:** Overview of approach.

Method	Sample	Aims	Analysis
Cognitive interviews (n=50)	25 (50% per language) sampled for maximum diversity	1: Cognitive evaluation and InDI^a^ revisions 2: Participant perspectives on attributions	1: Within- and between-interview analysis using Q-Notes 2: Qualitative analysis using grounded theory techniques
Previously collected validation data set (n=2583)	1518 (58.77%) in the United States 1065 (41.23%) in Canada	2: Intersectional psychometric evaluation	2: Exploratory factor analysis, exploratory structural equation modeling, and CFA^b^
Quantitative surveys	500 in Spanish^c^ 3000 in English^c^	2: Intersectional psychometric evaluation 3: Determine analytic utility of attributions	2: Multiple indicator multiple cause models and multigroup CFA 3: Descriptive statistics and multivariable regression models

^a^InDI: Intersectional Discrimination Index.

^b^CFA: confirmatory factor analysis.

^c^Quota sampling by race and ethnicity and sexual or gender minority status.

### Participants

Eligible participants will be aged ≥18 years and residing in the United States. For cognitive interviews (25/50, 50% English; 25/50, 50% Spanish), participants will be of any race and ethnicity and purposively sampled to achieve maximum diversity in gender, sexual orientation, race and ethnicity, socioeconomic status, age, and nativity. Quota sampling will be used for the quantitative surveys. The Spanish survey (n=500) will include 250 SGM and 250 non-SGM. The English survey (n=3000) will include non-Hispanic Black (1000/3000, 33%), non-Hispanic White (1000/3000, 33%), and Hispanic or Latino/a/x persons of any race (1000/3000, 33%), with 50% (250/500 for Spanish and 1500/3000 for English) of each group being composed of SGM. We will further stratify recruitment by gender to generate sample sizes of approximately 250 at each race and ethnicity *SGM* gender intersection (eg, White non-SGM women). Transgender and gender nonbinary respondents will be grouped by gender identity (eg, transgender men and transmasculine persons with men).

### Recruitment

Participants will be recruited using Facebook and Google advertisements in English and Spanish. Advertisements will also be placed on Black-, Latino/a/x-, and SGM-focused websites and circulated through relevant organizations. For the cognitive interviews, ads will link to the study information website. Interested individuals will complete a demographic screener and provide contact information. The bilingual study staff will contact selected participants to schedule an interview. For the quantitative survey, the ad will link to an eligibility screener with programmed quotas; individuals who meet eligibility criteria and whose recruitment category is open will be invited to participate and directed to the consent page. Multiple evidence-based strategies will be used to prevent and detect fraudulent respondents, including nondisclosure of eligibility criteria in ads, modest incentives, blocking responses from the same IP address, CAPTCHA (Completely Automated Public Turing test to tell Computers and Humans Apart), consistency and attention checks, and exclusion of records with implausible response times [60-62]. Using Qualtrics (SAP Inc) software, the English and Spanish surveys will be programmed as a single bilingual survey to prevent duplicate participation. Cognitive interview and survey participants will receive US $50 and US $15 electronic Amazon gift cards, respectively.

### Cognitive Interviews

Interviews will be conducted by trained research assistants using Health Insurance Portability and Accountability Act—compliant videoconferencing software (Zoom Health Insurance Portability and Accountability Act Private Mode). Verbal probing will be used to assess potential problems in the cognitive processes of question comprehension, information retrieval, judgment and estimation, and response [63]. At the start of the interview, participants will be sent a weblink to a questionnaire containing the unattributed InDI. Participants will respond to each item, and then the interviewer will ask them how they answered the question and why. Following best practices for cognitive interviewing, subsequent probes will ask the respondent to paraphrase the question, judge their confidence in the response, reflect on the accuracy of their recall, and indicate whether they had difficulty answering [64].

After completing the unattributed measures, participants will be presented with one of two attributed versions, one that requests either item-level attributions or overall attributions for each of the InDI measures (Multimedia Appendix 1). The interviewer will ask the respondent to complete the attribution items and then probe their responses as above. In addition, participants will be asked to share their perspectives on the importance of attributions (eg, “Did you prefer answering these questions with or without being asked for reasons why others mistreated you?”).

Interviewers will take notes directly into Q-Notes software, developed by the National Center for Health Statistics for the analysis of cognitive interviewing data [65]. Q-Notes is designed to facilitate real-time cross-site collaborations to evaluate instruments in multiple languages. This will facilitate the rapid analysis of data for aim 1 and subsequent revisions to improve the clarity and completeness of the InDI items. Interviews will also be recorded, transcribed verbatim, and translated into English if needed.

### Quantitative Surveys

The self-administered survey will take approximately 20 minutes to complete.

#### Intersectional Discrimination Index

All Spanish-language participants will receive the unattributed InDI (Multimedia Appendix 1), with potential modifications based on cognitive interview findings. For the English survey, we will use the block-randomization feature in Qualtrics to implement a split-ballot design: 1000 participants will receive each of the unattributed, item-level attributed, or overall attributed versions of the InDI.

#### Demographics

Age, sex assigned at birth, current gender identity, race, ethnicity, immigration history, education, income, sexual orientation, geographic region, and community size (eg, urban and rural) data will be collected.

#### Health Outcomes

To permit psychometric evaluation of these novel instruments (aim 2) and comparisons between attribution methods (aim 3), analyses in the current proposal will focus on two of the most well-established health consequences of perceived discrimination: psychological distress and self-rated general health [15]. Psychological distress will be measured using the 6-item K6 measure developed by Kessler et al [66]. The K6 was developed to estimate the prevalence of serious mental illness and has shown good sensitivity and excellent specificity in US population samples when dichotomized at a score of 13/24 or above and compared with Diagnostic and Statistical Manual of Mental Disorders-IV diagnoses via structured clinical interviews [66,67]. Self-rated general health, a robust predictor of morbidity and mortality [68], will be assessed using a standard question from the Behavioral Risk Factor Surveillance System and other federal surveys (“Would you say in general that your health is—excellent, very good, good, fair, or poor?”). To facilitate secondary analyses of these data focused on a wider range of health outcomes, the survey will also collect data on substance use (nicotine, alcohol, and illicit drugs), hypertension, and diabetes.

### Analysis Plan

#### Aim 1: Cognitive Evaluation of the InDI Measures in English and Spanish

Using sorting features in the Q-Notes software, we will first analyze detailed interview notes at the within-interview level (to capture response errors). Next, we will compare data on each survey item across interviews to evaluate consistency in understanding what the question intends to capture. Finally, we will sort data by participant subgroups (eg, by language, race and ethnicity, and SGM status individually) to identify potential response biases. Two analysts will complete each of these steps independently, meeting to compare analysis notes and generate a list of potential modifications at the end of each stage. Potential modifications to address identified problems with instructions, items, or response options will be reviewed by all team members; if modifications are made, the revised measures will be evaluated with five new cognitive interviews in each language.

#### Aim 2: Psychometric Evaluation of the InDI Measures Across Languages and Intersecting SSPs

Analyses will be conducted in MPlus (Muthén & Muthén) and Stata (StataCorp LLC). As a first step, we will conduct exploratory factor analysis, exploratory structural equation modeling, and confirmatory factor analysis (CFA) of the InDI-D and InDI-M in our previously collected data, using split-halves of the sample by country (n=1065 and n=1518). These analyses will help us establish the configural and metric structures of the two enacted discrimination measures. We previously used this approach to assess the psychometric properties of the InDI-A, finding support for its hypothesized unidimensionality. At that time, we opted not to conduct factor analyses of the enacted discrimination measures, with the rationale that their items are causal-formative indicators that aggregate to form a construct, rather than items that reflect the level of an underlying construct and should necessarily correlate [69]. Nevertheless, existing research demonstrates that discrimination scales do show strong interitem correlations and factor structures [47], likely reflecting both respondent characteristics that determine perception and self-reporting of discrimination, as well as the social clustering of discrimination. Furthermore, the assessment of configural, metric, and scalar structures of the InDI measures should precede the evaluation of measurement equivalence across intersectional groups, thereby determining whether the discrimination burdens they estimate can be meaningfully compared across groups [47]. We will evaluate the goodness of fit for CFA with parsimony, incremental, and absolute indices [70]. If substantive changes are made to the InDI items in aim 1, we will instead conduct the exploratory factor analysis, exploratory/confirmatory factor analysis, and CFA using randomly selected samples of the new survey data (n=200 each).

Once the configural and metric structures of the InDI measures are established, we will assess their scalar structures. We will estimate the Loevinger H coefficient to determine whether scales reflect the Mokken model (ie, those endorsing severe items are more likely to endorse less severe items) [71]. This will be followed by the estimation of item response theory models [72]; item discrimination and item difficulty will be estimated to assess how well the InDI measures tap their underlying traits. The results will be graphically displayed in a Wright map, item characteristic curves, a test information function plot, and a test characteristic curve graph.

Next, we will use originally collected survey data to assess differential item functioning and measurement equivalence, using Multiple Indicator Multiple Cause (MIMIC) models and multigroup CFA (mCFA), respectively. These approaches are complementary: mCFA compares the full measurement model across groups, whereas MIMIC is generally limited to testing for differences in item difficulty (thresholds for endorsement). However, mCFA estimates parameters separately for groups defined by a single categorical variable and requires a sufficient sample size for each group, whereas MIMIC uses a single model for the full sample, making it more efficient and permitting isolation of reasons for differential item functioning [73,74]. Therefore, we will use the MIMIC methods across a range of SSPs of interest and the mCFA methods across the intersectional quota-sampled strata. We will include gender, sexual orientation, race and ethnicity, socioeconomic status, age, and nativity as covariates in the MIMIC model for each measure.

We will use mCFA to determine whether the configural, metric, and scalar structures of the InDI measures are equivalent across (1) language (English vs Spanish) and (2) the 12 intersectional race and ethnicity*SGM*gender sample strata. Achieving equivalence across all these scale structures is necessary for the InDI measures to generate meaningful cross-group comparisons. After estimating the baseline models for each group, we will test configural equivalence across language and intersectional strata. We will then assess the metric equivalence of the scales by examining whether factor loadings vary across these groups by comparing the fit of the metric models with those of the configural models. To assess scalar equivalence, item thresholds will be tested for their equivalence among the same groups. Formal comparisons will be carried out by comparing the fit of the scalar models with those of the metric models. To compare less (eg, configural) and more restrictive (eg, metric and scalar) models, we will use a reduction ≥0.002 in the value of the comparative fit index as an unbiased indication of lack of equivalence, given the sensitivity of *P* values to large sample sizes [75]. We will also assess the partial invariance of the InDI measures. If needed (eg, because of numerous large modification indices), the alignment method will be used as an alternative to assess measurement equivalence [76].

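### The MIMIC covariates include nativity and ethnicity but not survey language or questionnaire version, so a pooled model would report part of a translation effect as nativity or Latino/a/x item bias

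*Protocol article*

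**What the plan says.** The Objectives make "measurement equivalence across language and intersecting SSP" part of Aim 2. The Aim 2 analysis plan opens this step with "Next, we will use originally collected survey data to assess differential item functioning and measurement equivalence" and names two tools, MIMIC and multigroup confirmatory factor analysis (mCFA).

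MIMIC is justified as follows: "MIMIC uses a single model for the full sample, making it more efficient and permitting isolation of reasons for differential item functioning". The work is then divided: "we will use the MIMIC methods across a range of SSPs of interest and the mCFA methods across the intersectional quota-sampled strata". The MIMIC covariates are given in one sentence: "We will include gender, sexual orientation, race and ethnicity, socioeconomic status, age, and nativity as covariates in the MIMIC model for each measure".

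For mCFA, the structures are to be tested as "equivalent across (1) language (English vs Spanish) and (2) the 12 intersectional race and ethnicity*SGM*gender sample strata", and this includes thresholds: "To assess scalar equivalence, item thresholds will be tested for their equivalence among the same groups".

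Three other places bear on the point:
- Table 1 puts the 500 Spanish and 3000 English surveys in one row, with MIMIC and mCFA as its Aim 2 analyses.
- Quantitative Surveys, Intersectional Discrimination Index, gives every Spanish respondent the unattributed version. English respondents are randomised to three versions, 1000 each.
- The Introduction section on the index cites evidence that Latino/a/x respondents answer discrimination measures differently according to survey language and acculturation.

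**The concern.** MIMIC is chosen partly because it can separate the reasons for DIF. It can do so only for reasons that are in the model. Survey language is a reason that the article itself expects, yet the covariate list leaves it out and includes two of its close correlates, nativity and Latino/a/x ethnicity. An item whose Spanish wording behaves differently would push its direct effect onto those two variables.

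Version adds to this. In the pooled data, being on the unattributed version is tied to answering in Spanish. Any effect of asking for attributions would therefore travel the same way.

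What is at stake is how an item is labelled. A translation fault could be read as a difference between foreign-born and US-born respondents, or between Latino/a/x and other respondents, and these call for different responses.

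**Working it through.** **The plan's own figures.** Sample Size gives 250 per stratum. 3 racial and ethnic groups x 2 SGM levels x 2 genders = 12 strata, and 12 x 250 = 3000, as stated. The three versions at 1000 each also give 3000.

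**Inputs from the article.** Black 1000, White 1000, English Latino/a/x 1000, Spanish 500. Unattributed share: 1 in Spanish, 1/3 in English.

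**Assumptions not in the article.** All Spanish respondents are Latino/a/x. SGM status and gender are balanced in every group. The foreign-born share is 10% in the Black and 5% in the White sample. Item effects are on a linear scale, and age and socioeconomic status are left out. Let s be the foreign-born share in the Spanish sample and e the share in the English Latino/a/x sample.

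**Language omitted.** By the omitted-variable formula, the share of a language effect that lands on nativity is the covariance of language with nativity within racial and ethnic groups, divided by the variance of nativity within those groups.

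- Numerator: language varies only among the 1500 Latino/a/x respondents, one third of them Spanish. This gives 1500 x (1/3)(2/3) x (s - e) = 333.3(s - e).
- Denominator: 1000(0.10)(0.90) + 1000(0.05)(0.95) + 1500 f(1 - f) = 137.5 + 1500 f(1 - f), with f = (500s + 1000e)/1500.
- Share on Latino/a/x (against White): 1/3 - (nativity share) x (f - 0.05).

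Worked case, s = 80% and e = 30%: f = 700/1500 = 0.467. Numerator 166.7; denominator 137.5 + 373.3 = 510.8. Nativity takes 166.7/510.8 = 0.33. Latino/a/x takes 0.333 - 0.326 x 0.417 = 0.20.

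| s / e | to nativity | to Latino/a/x |
|---|---|---|
| 60% / 30% | 0.20 | 0.26 |
| 80% / 30% | 0.33 | 0.20 |
| 80% / 50% | 0.20 | 0.22 |
| 90% / 20% | 0.46 | 0.16 |
| 95% / 30% | 0.42 | 0.14 |
| 50% / 50% | 0 | 0.33 |

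The first five rows give the ranges 0.20-0.46 and 0.14-0.26. Corner combinations of the same limits go a little further. At 60%/50%, f = 0.533 and nativity takes 33.3/510.8 = 0.07, leaving 0.333 - 0.065 x 0.483 = 0.30 on Latino/a/x. At 95%/20%, f = 0.45 and nativity takes 250/508.75 = 0.49, leaving 0.14.

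**Version omitted.** The expected unattributed share is 1/3 + (2/3) x (Spanish), so each leakage is two thirds of its language counterpart. Over the five pairs this is 0.13-0.31 to nativity and 0.09-0.18 to Latino/a/x, and in the 50%/50% case 0 and 0.22. Equivalently, (500 + 333)/1500 = 55.6% of pooled Latino/a/x respondents are unattributed, against 33.3% of the others. Within English alone, version is randomised and the leakage is zero in expectation.

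**After the change.** With language in the model, nativity and ethnicity no longer carry either effect in expectation. With language alone, however, the language coefficient carries 1 - 1/3 = 0.667 of any version effect. With both in the model they can be separated. Version varies by randomisation within English, and the English unattributed third is the like-for-like comparator for the Spanish sample.

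**Product terms.** Suppose a bias of 1 unit is confined to one of 12 equal strata, for example Black SGM women. A main-effects fit shows 0.25 for Black (1/4), 0.17 for SGM (1/6) and 0.17 for women (1/6). In the affected stratum it fits 1/4 + 1/6 + 1/6 - 2/12 = 0.42. MIMIC results are thus single-axis summaries. The 12-stratum mCFA tests that stratum's thresholds directly, at 250 per stratum against the stated minimum of 200.

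**The case against.** **Pooling is not stated outright.** In the article, "MIMIC uses a single model for the full sample" contrasts MIMIC with mCFA in general terms. The covariate list is not declared exhaustive, and this is a condensed article. If MIMIC were fitted to the English survey alone, both leakages would vanish. This stands as a caveat and lowers confidence. Still, nothing limits MIMIC to English or to one version, and Table 1 points to both surveys.

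**Language is not neglected in Aim 2.** The mCFA tests English against Spanish, including thresholds, and 25 Spanish cognitive interviews precede the survey. A reader might infer that a badly translated item would go unnoticed or would lead to the wrong revision. The article does not support that: no passage ties item revision to a MIMIC coefficient, and it presents the two methods as complementary. But the mCFA does not change the MIMIC estimates for nativity and ethnicity. As written, it also compares an all-unattributed Spanish sample with an English sample that is two-thirds attributed (2000/3000) and two-thirds non-Latino/a/x (2000/3000). It therefore cannot by itself say which of these lies behind a difference.

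**Intersections.** A reader might infer from the absence of product terms that intersectional DIF is missed. It is not. The article gives that task to mCFA across the 12 strata and sizes the survey for it.

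**Version.** A reader might infer that leaving version out biases every MIMIC coefficient. It does not, because version is randomised within English. The bias enters only through pooled Spanish respondents.

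**Size.** The nativity shares are assumed, and with equal nativity in the two samples nearly nothing need go to nativity. That is correct, but the effect then moves to Latino/a/x ethnicity (0.33) and does not disappear.

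**Conclusion.** The point holds in a limited form. If the two surveys are pooled in MIMIC, as the text most naturally reads, the stated covariates cannot separate translation from nativity and ethnicity. Roughly a fifth to nearly a half of a language effect on an item would be attributed to nativity, and about a seventh to a quarter to Latino/a/x ethnicity, over the five assumed pairs of foreign-born shares. For version the leakage is two thirds of that. These fractions rest on a linear approximation and on nativity shares that the article does not give, so they show the order of the problem and do not predict its size in the data.

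The finding does not extend to intersectional DIF or to the language comparison as a whole, both of which have planned tests. It is an improvement available at no real cost. Confidence is moderate.

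**What to change.** Add survey language and questionnaire version (unattributed, item-level, overall) as covariates to every MIMIC model that pools the two surveys, and test their direct effects on the items alongside those of the listed covariates. Alternatively, restrict the pooled model to unattributed respondents and include language. That leaves 500 + 1000 = 1500 of 3500 respondents, so the first option keeps more information. If MIMIC is meant for the English survey only, say so; the language and version terms are then not needed to protect the nativity and ethnicity estimates.

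State also that MIMIC results describe single axes and are to be read with the 12-stratum mCFA. No product terms are needed.

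Both variables are known by design, so nothing more has to be collected. The cost is model specification and a few additional direct-effect tests per item.
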